### **5.4. Inclusion and Exclusion Criteria**

#### **Inclusion Criteria**

- (1) Women aged 13-65 years and Diagnosed with BN according to DSM-5 criteria during a clinical interview.
- (2) Having a BMI over 17.5 kg/m^2.
- (3) Using computers, tablets, smartphones, etc, daily, with access to the internet and the minimum necessary information and communications technology skills.
- (4) No history of CBT in the last 2 years.

#### **Exclusion criteria:**

- (1) Serious mental disorders such as organic brain disorders, psychotic disorders, and drug dependence.
- (2) Imminent risk of suicide.

(3) Repeated engagement in antisocial behavior.

(4) Serious progressive physical disease.

(5) Difficulty in exposure to feared objects due to severe stress reactions or dissociation symptoms due to acute stress disorder or posttraumatic stress disorder.

### **5.5. Randomization and Blinding**

An independent data management team at Fukui University randomizes all participants to either the intervention or control group using the UMIN Medical Research Support (Case Registration and Allocation) System Cloud (UMIN System Cloud) and employs forced balanced randomization. This randomization sequence is concealed from both participants and their primary care physicians to ensure impartiality. Furthermore, an independent evaluation team at Fukui University remains blinded to the group assignment of the participants being evaluated to maintain the integrity of the study outcomes.

### **5.6. Measures**

Potential participants who apply for the study provide their name, age, sex assigned at birth, height, recent weight, educational background, employment history, employment status, marital status, family history of mental illness, medical history, current medications and dosages, and information about the devices (smartphone, personal computer [PC], tablet PC, etc.) they are using for the study through an online data

collection system.

#### **5.6.1. Eligibility Screening and Structured Clinical Interviews**

Eligibility assessments are conducted by experienced clinicians or researchers via face-to-face, telephone, or video conference interviews. A semi-structured diagnostic interview, the Mini-International Neuropsychiatric Interview (M.I.N.I.), is administered to assess for the presence of comorbid conditions.

#### **5.6.2. Outcomes**

The study assesses various outcomes, such as eating disorder severity, comorbid depression and anxiety, quality of life (QOL), satisfaction with the treatment, and the therapeutic alliance.

#### **5.6.3. Primary Outcome**

The primary outcome, the weekly combined frequency of binge eating and compensatory behavior episodes, is assessed at baseline and 12 weeks post-intervention. The independent assessor team at the University of Fukui measures the primary outcome via telephone.

#### **5.6.4. Secondary Outcomes**

- Weekly frequency of binge eating episodes: The independent assessor team asks the weekly frequency of binge episodes via telephone.
- Weekly frequency of compensatory behavior episodes: The independent assessor team asks the weekly frequency of compensatory behavior episodes via telephone.

**5.6.5. Eating Disorder Examination Questionnaire 6.0, EDE-Q:** The EDE-Q is a widely used self-report instrument for assessing the severity and frequency of symptoms associated with eating disorders. It comprises 28 items that evaluate eating behaviors, attitudes, and concerns over the last 4-week period. Responses are rated on a 7-point Likert scale, ranging from 0 (never) to 6 (daily). The EDE-Q is composed of four subscales: restraint, eating concern, shape concern, and weight concern. The Japanese version of the EDE-Q has demonstrated adequate internal consistency and good reliability and validity for these four factors. The severity of each subscale is represented by the total score for that subscale, and the EDE-Q global score is derived from the average of the subscale scores. Among a sample of 727 Japanese female university students (age: M = 19.32, SD = 1.08; BMI: M = 20.46, SD = 2.56), the mean (SD) EDE-Q global score was 1.51 (1.02). Mean (SD) scores for the restraint, eating concern, shape concern, and weight concern subscales were 0.86 (1.10), 0.58 (0.82), 2.45 (1.52), and 2.13 (1.41), respectively (Mitsui, 2013). In the present study, the EDE-Q global score is designated as secondary outcomes.

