### **6.3. Exploratory Analyses and Additional Statistical Tests**

To assess treatment satisfaction and therapeutic alliance, the post-treatment mean values will be calculated for the intervention group. To evaluate baseline differences between the two groups, independent samples t-tests, chi-square tests, and Fisher's exact tests will be used. For the binary outcome of remission in bulimia nervosa (BN), a chi-square test will be employed to assess the significance of the odds ratio (OR). The criteria for remission will be determined using the cutoff values of the EDE-Q score, 2.34 or 2.80.

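### The EDE-Q scoring rule (subscale totals, then averaged) does not fit the protocol's own EDE-Q norms or its exploratory remission cutoffs

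*Protocol*

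**What the plan says.** Section 5.6.5 of the protocol describes the EDE-Q as a 28-item questionnaire with responses from 0 to 6. It names four subscales: "The EDE-Q is composed of four subscales: restraint, eating concern, shape concern, and weight concern". Scoring has two steps. First, "The severity of each subscale is represented by the total score for that subscale". Second, "the EDE-Q global score is derived from the average of the subscale scores". No score range is given, and neither is the number of items in each subscale.

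The same paragraph quotes norms from 727 Japanese female university students. The global mean is 1.51 (SD 1.02), and the "subscales were 0.86 (1.10), 0.58 (0.82), 2.45 (1.52), and 2.13 (1.41), respectively". The global score is named there as a secondary outcome, and section 1 lists it among the secondary confirmatory outcomes.

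Section 6.3, on exploratory analyses, sets the remission criterion by "the cutoff values of the EDE-Q score, 2.34 or 2.80". Section 6.2 applies the primary model to the secondary outcomes. Section 6.1 says that model will report Cohen's *d* and a least squares mean difference with a 95% CI.

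**The concern.** Where the protocol gives a total score for another instrument, it is a sum of items. An analyst who follows section 5.6.5 to the letter would therefore sum the items of each subscale and average the four sums. The result would not share a scale with the norms printed beside the rule or with the cutoffs in section 6.3. Nothing in the protocol converts a sum back to the 0 to 6 scale, and no stated EDE-Q range would expose the mismatch.

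Two results are at stake. The remission comparison would apply a 0 to 6 threshold to scores that run several times higher. The EDE-Q mean difference and its confidence interval would be on a scale that the protocol does not declare and that cannot be set against its norms.

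**Working it through.** **Inputs.** From section 5.6.5: items scored 0 to 6; 28 items; four subscales; subscale norms 0.86, 0.58, 2.45 and 2.13; global norm 1.51 (SD 1.02). From section 6.3: cutoffs 2.34 and 2.80. The number of items per subscale, *k*, is not stated. Equal subscales of *k* = 2 to 7 are shown as an assumption; 28/4 = 7 is the ceiling for equal subscales if every item is used once.

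**Step 1: reproduce the stated norm.** (0.86 + 0.58 + 2.45 + 2.13)/4 = 6.02/4 = 1.505, which agrees with 1.51. This confirms the averaging step only. It would come out the same if the four figures were item means or totals, so it does not settle the metric.

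**Step 2: what a total score means in this protocol.**
- PHQ-9 (section 5.6.6): nine items on a 4-point scale, total 0 to 27 = 9 × 3.
- GAD-7 (section 5.6.6): seven items on a 4-point scale, total 0 to 21 = 7 × 3.
- WAI-SF (section 5.6.7): 12 items on a 7-point scale, total 12 to 84 = 12 × 1 to 12 × 7.

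Each is a sum.

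**Step 3: test both readings of the norms and cutoffs.** If they are item means, an item-mean global of *m* becomes *k* × *m* under the written rule. If they are already totals, dividing by *k* gives the item mean that they imply.

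| *k* | Global range as written (0 to 6*k*) | Average student as written, if norms are item means (*k* × 1.505) | Student item mean, if norms are totals (1.51/*k*) | Cutoffs as item means, if applied to totals (2.34/*k*, 2.80/*k*) |
|---|---|---|---|---|
| 2 | 0–12 | 3.010 | 0.755 | 1.170, 1.400 |
| 3 | 0–18 | 4.515 | 0.503 | 0.780, 0.933 |
| 4 | 0–24 | 6.020 | 0.378 | 0.585, 0.700 |
| 5 | 0–30 | 7.525 | 0.302 | 0.468, 0.560 |
| 6 | 0–36 | 9.030 | 0.252 | 0.390, 0.467 |
| 7 | 0–42 | 10.535 | 0.216 | 0.334, 0.400 |

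- *Norms and cutoffs as totals.* At 5 to 7 items, the average student would have an item mean of about 0.2 to 0.3 on a 0 to 6 scale, and remission would require an item mean of about 0.3 to 0.6. This is possible arithmetically but implausible.
- *Norms and cutoffs as item means.* The cutoffs lie (2.34 − 1.51)/1.02 = 0.81 SD and (2.80 − 1.51)/1.02 = 1.26 SD above the student mean, and at 39% and 47% of the 0 to 6 range. This is coherent.

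**Step 4: consequence of scoring as written.** With two items per subscale, the average student scores 3.01, already above both cutoffs. The result does not need equal subscales: if every subscale has at least two items, each of the four terms at least doubles, so the average is at least 2 × 1.505 = 3.01. Taking remission as a score below the cutoff, a participant with an item mean between 2.34/*k* and 2.34 (or between 2.80/*k* and 2.80) would be wrongly counted as not in remission.

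**Step 5: what would not change.** With equal item counts, totals multiply every global score by the same *k*. The mean difference and its confidence limits are multiplied by *k*; the p-value and Cohen's *d* stay the same.

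**The case against.** The strongest reply is that this is loose wording. The paragraph names the instrument version, cites its source and the Japanese psychometric study, and prints norms next to the rule, so an analyst would probably notice that raw sums do not match. That is fair. Nothing in the protocol shows that sums were used, and a reader should not infer that the analysis was scored wrongly. The written rule is still inconsistent with the figures around it.

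Several stronger readings are tempting, and the protocol does not support them:

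- *That the 1.505 check proves the norms are item means.* It does not (step 1). The 0 to 6 metric of the norms and cutoffs is a plausibility inference from step 3.
- *That almost no participant could reach remission if scored as written.* The protocol gives no patient EDE-Q mean or SD, so this cannot be computed. Even in the norm sample, under a rough normal approximation with mean 1.51 and SD 1.02, about 12% to 18% would fall below item means of 0.33 to 0.56, the cutoff equivalents at 5 to 7 items.
- *That summing gives longer subscales more weight in the global score.* This requires unequal subscale lengths, which the protocol does not give.
- *That a confirmatory result is invalid.* Remission is listed among the exploratory analyses, and with equal item counts the EDE-Q test and standardised effect are unaffected. The primary outcome does not use the EDE-Q.

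It is also right that no printed figure is miscalculated. The fault lies in the scoring definition.

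**Conclusion.** The point stands as an inconsistency in a stated scoring rule. Averaging the subscales agrees with the norms; defining each subscale by its total does not fit the norms or the cutoffs. With two or more items in every subscale, the average norm-sample student would exceed both remission cutoffs under the written rule (3.01 at the least; 7.5 to 10.5 with 5 to 7 items each). Remission would be misclassified, and the EDE-Q mean difference and its CI would be on a different scale. With equal item counts, the global p-value and Cohen's *d* would be unchanged.

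This rests on two assumptions: that the norms and cutoffs are 0 to 6 item means, which is inferred, and that each subscale has at least two items. The effect is confined to one secondary outcome and one exploratory analysis, and it becomes real only if the rule was applied literally.

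**What to change.** In section 5.6.5, replace the scoring rule with: each subscale score is the mean of its items (0–6); the global score is the mean of the four subscale scores (0–6). State in section 6.3 that the remission cutoffs apply to that global score.

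Section 9 dates the completion of analysis to December 30, 2024, so the check may be retrospective: verify that the scoring used, or already used, for the EDE-Q and remission analyses follows this rule, and recompute those results if it does not. The cost is one or two sentences and a check of the scoring code.

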**5.6.6. Secondary Exploratory Outcomes**

- **The Patient Health Questionnaire 9 items (PHQ-9):** The PHQ-9 is a brief self-report measure designed to screen for major depressive disorder (MDD). It is based on the diagnostic criteria for MDD as outlined in the DSM-IV and assesses the severity of depressive symptoms. A diagnosis of MDD is supported if five or more of the nine DSM-IV criteria for MDD have been present for at least half of the days during the past two weeks and at least one of the symptoms is either depressed mood or

loss of interest or pleasure. The PHQ-9 consists of nine items rated on a 4-point Likert scale, with a total score range of 0 to 27. The interpretation of PHQ-9 scores is categorized into five levels of severity: minimal (0-4), mild (5-9), moderate (10-14), moderately severe (15-19), and severe (20-27).

The psychometric properties of the Japanese version of the PHQ-9 have been well-established.

- **The Generalized anxiety disorder 7 item (GAD-7):** The GAD-7 is a brief self-report measure designed to screen for generalized anxiety disorder (GAD). It is based on the diagnostic criteria for GAD outlined in the DSM-IV and assesses the severity of GAD symptoms. The GAD-7 consists of seven items rated on a 4-point Likert scale, with a total score range of 0 to 21. A cutoff score of 10 or higher is commonly used to identify individuals with probable GAD. The interpretation of GAD-7 scores is categorized into four levels of severity: minimal (0-4), mild (5-9), moderate (10-14), and severe (15-21). The psychometric properties of the Japanese version of the GAD-7 have been well-established.
- **The EuroQol 5 dimensions 5-level (EQ-5D-5L):** The EQ-5D-5L is a quality-of-life measure that assesses five dimensions of health: mobility, self-care, usual activities, pain/discomfort, and anxiety/depression. Responses are rated on a 5-point Likert scale ranging from 1 (no problems) to 5 (extreme problems). A health index score can be derived from the EQ-5D-5L, ranging from 0 (death) to 1 (full health). A Japanese valuation of EQ-5D-5L was developed to create the QOL value for a quality of adjusted life year using a national sample of 1,026 individuals.
- **The Brunnsviken Brief Quality of Life Scale (BBQ):** The BBQ was developed to measure subjective QOL. It consists of 12 items covering six life areas: Leisure, View on life, Creativity, Learning, Friends

and Friendship, and View on self. For each life area, respondents rate their satisfaction and importance on a 5-point Likert scale ranging from 0 (strongly disagree) to 4 (strongly agree). The total BBQ score can range from 0 to 96. The validity of the Japanese version of the BBQ has been demonstrated by our research group.

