| C: Control      | 
 
● 12 weeks waiting time
 
                                                                                                                                                                                                                                                                                                                                                                                                                                                                                                                                                                                                                                                                                                                                                                                                                                                                                                                                      |
| O: Outcome      | 
Primary Confirmatory
 
 
● Number of binge eating and compensatory behavior episodes
 
 
Secondary Confirmatory
 
 
● Number of binge eating episodes
 
● Number of compensatory behavior episodes
 
● Global eating psychopathology (EDE-Q)
 
● Comorbid depression (PHQ-9)
 
● Comorbid anxiety (GAD-7)
 
● Quality of life (EQ-5D-5L)
 
● Well-being (BBQ)
 
 
Additional Assessments
 
 
● Working alliance in the treatment (WAI-SF)
 
● Satisfaction for the treatment (CSQ)
 
                                                                                                                                                                                                                                                                                                |

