## 6. Planned Statistical Analysis

Statistical analyses will be performed using SPSS Statistics software (version 29; IBM Corp) or R Statistics.

Analyses will be conducted based on the intention-to-treat principle (ITT), in accordance with the CONSORT

2010 checklist. All *P*-values will be two-tailed, and a *P*-value < .05 will be considered statistically significant.

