### **6.2. Secondary Confirmatory Analyses**

Secondary analyses will be conducted using the same statistical model as the primary analysis to evaluate the multifaceted effects of the intervention through secondary outcomes (eating disorder severity, depression,

anxiety, and quality of life). The analyses will examine differences between groups as well as changes over time.

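### PHQ-9, GAD-7, EQ-5D-5L and BBQ are confirmatory secondaries in section 1 (and by domain in 6.2) but exploratory in 5.6.6, while section 6 tests every outcome at .05

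*Protocol*

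**What the plan says.** The outcome row of the table in section 1 has a block headed "Secondary Confirmatory" with seven entries: binge episodes, compensatory episodes, EDE-Q, "Comorbid depression (PHQ-9"), "Comorbid anxiety (GAD-7"), "Quality of life (EQ-5D-5L") and BBQ.

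Section 5.6 divides them differently. Sections 5.6.4 and 5.6.5 give binge frequency, compensatory frequency and the EDE-Q global score as secondary outcomes. Section 5.6.6 then opens a separate heading, "Secondary Exploratory Outcomes", and puts PHQ-9, GAD-7, EQ-5D-5L and BBQ under it.

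Section 6.2, whose own heading calls its analyses confirmatory, applies the primary model "to evaluate the multifaceted effects of the intervention through secondary outcomes" and names eating disorder severity, depression, anxiety and quality of life as the domains. Section 6.3, the exploratory analyses, covers satisfaction, alliance, baseline comparisons and EDE-Q remission. It does not mention the four instruments.

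Section 6 gives the only decision rule: "All *P*-values will be two-tailed, and a *P*-value < .05 will be considered statistically significant".

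**The concern.** The two labels license different conclusions from the same p-value. If PHQ-9 came out at P = .04, section 1 would allow it to be reported as a confirmed effect on depression, while section 5.6.6 would allow it only as a lead for later work. The analysis section does not settle the matter: it treats the domains as confirmatory and gives the exploratory label no counterpart.

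The confirmatory reading also carries an error-rate cost. The protocol attaches the word confirmatory to a family of seven outcomes and sets .05 for each, with no adjustment, testing order or dependence on the primary result. At stake is how far the secondary claims can be relied on.

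**Working it through.** **The plan's own figures.** The protocol states no error rate for the secondary family. Its only calculation at the .05 level is the sample size in section 6.6 (d = 0.9, two-sided 0.05, 80% power). It reproduces: the exact t-test power is 79.2% at 20 per group and 81.2% at 21, so 21 is the minimum, and 21 / (1 − 0.30) = 30. That level belongs to the single primary comparison.

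**The labels side by side.**

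| Outcome | Section 1 | Sections 5.6.4–5.6.6 | Section 6.2 |
|---|---|---|---|
| Binge frequency | confirmatory | secondary | confirmatory (eating disorder severity) |
| Compensatory frequency | confirmatory | secondary | confirmatory (eating disorder severity) |
| EDE-Q global | confirmatory | secondary | confirmatory (eating disorder severity) |
| PHQ-9 | confirmatory | exploratory | confirmatory (depression) |
| GAD-7 | confirmatory | exploratory | confirmatory (anxiety) |
| EQ-5D-5L | confirmatory | exploratory | confirmatory (quality of life) |
| BBQ | confirmatory | exploratory | by inference only |

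Section 6.2 names domains, not instruments, so its column is a mapping. For BBQ the mapping is weakest: section 1 calls it well-being, and it falls under 6.2 only because the text under 5.6.6 describes it as a quality-of-life measure.

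**Error rate over the family.** Inputs: a level of 0.05 per test (section 6); k = 7 (section 1) or k = 3 (the outcomes outside 5.6.6). All k null hypotheses are taken as true.

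- Independent tests: 1 − (1 − 0.05)^k.
  - k = 7: 1 − 0.95^7 = 1 − 0.698 = 0.302.
  - k = 3: 1 − 0.95^3 = 1 − 0.857 = 0.143.
- Any dependence (Bonferroni bound): 7 × 0.05 = 0.35 and 3 × 0.05 = 0.15.
- Correlated tests: the documents give no correlations, so a common value r is assumed. Simulation of 1,000,000 sets of equicorrelated normal test statistics gives:

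| Assumed r | k = 7 | k = 3 |
|---|---|---|
| 0.3 | 27% | 14% |
| 0.5 | 23% | 13% |
| 0.7 | 18% | 11% |
| 0.9 | 11% | 8% |

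For two-sided tests on jointly normal statistics, the independent case is the maximum (Šidák inequality), so 30% and 14% are upper cases in that setting.

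- Only false results favouring the intervention, independent tests, k = 7: 1 − 0.975^7 = 0.162.

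**With control.** Holm starts at 0.05/7 = 0.0071 for seven outcomes, or 0.05/3 = 0.0167 for three. Either holds the family at 5% or below. If testing also waits for a significant primary, the 5% covers the primary and the confirmatory secondaries together. When the primary null is true, a false secondary claim first needs a false primary result; when it is not true, Holm limits the rest.

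**The case against.** Several objections have force.

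- **Independence is unrealistic.** Binge and compensatory frequency are the two parts of the primary composite. EQ-5D-5L has an anxiety/depression dimension that overlaps PHQ-9 and GAD-7, and BBQ and EQ-5D-5L both measure quality of life. A reader might take 30% as the actual rate, but the documents' own outcome definitions argue against that. The correlated range is the fairer summary, and its correlations are assumed.
- **The primary is untouched.** A reader might infer that the trial's effectiveness conclusion is inflated. It is not: section 6.1 rests that conclusion on one outcome, which keeps its own 5%.
- **Multiplicity detail may sit in an analysis plan that is not shown.** This is right as far as a missing procedure goes, and the absence of one is not the point here. The protocol itself calls these analyses confirmatory and itself says that P < .05 "will be considered statistically significant" for all P-values. That is a stated rule, and together with the label conflict it stands.
- **Nothing shows that 5.6.6 is the intended label.** Correct. Section 1 and, by domain, section 6.2 say confirmatory, and section 6.3 omits the four scales.
- **Relabelling alone does not cure the problem.** Also correct: three unadjusted tests still give about 14% under independence.
- **Timing.** Section 9 gives analysis completion as December 30, 2024, and the reference list carries access dates in January 2025. A choice made now is not prespecified. A reader might go on to infer that labels were changed in the light of results; the documents do not show that.

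**Conclusion.** The contradiction is real and lies in current text. The one change that section 6.1 describes, from ANCOVA to a mixed model, does not explain it. Under the confirmatory reading, the chance of at least one false secondary claim is about 18% to 27% for assumed common correlations of 0.7 to 0.3, with 30% as the upper case under independence. Under the narrower 5.6.6 reading without adjustment it is at most 14% for independent or jointly normal tests. These figures assume that every null in the family is true and count errors in either direction. The problem is limited to what may be claimed from secondary outcomes, but it should be corrected because the same p-value now supports two different statements.

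**What to change.** 1. Bring sections 1, 5.6.6 and 6.2 to one classification, naming instruments in 6.2. If the version finalised on June 22, 2022 or the protocol paper of September 19, 2023 (dates in section 9) settles the point, use it. If neither does, take the narrower 5.6.6 reading, because it can only reduce confirmatory claims and cannot rescue a result.
2. Test whichever secondaries remain confirmatory by Holm, or in a stated fixed order, and only after a significant primary.
3. Report the others as estimates with 95% confidence intervals, labelled exploratory.
4. State the date of the change and that it follows the analysis completion date in section 9.

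The cost is wording and a Holm step on p-values already planned; no new data or participants are needed. The downside is that fewer secondary results can be called confirmed.
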